### Data collection

Primary outcomes include anthropometric and clinical examinations, self-reported and objectively measured PA, self-reported diet and self-reported psychosocial health, while secondary outcomes include age, sex, socioeconomic status (SES)and school. Standard procedures to assess the interventions’ health effects on markers for NCD risk factors will be conducted by well-trained professional staff (eg, biokineticists), who will adhere to standardised, quality-controlled protocols established during previous work of the research group in the area.

Anthropometric measurements: Body weight will be measured on a digital weighing scale and body height against a stadiometer with back erect and shoulders relaxed. Body mass index (BMI) will be calculated as weight (kg)/height (m),^2^ and additionally, BMI-for-age stratified by sex will be determined for children according to WHO growth charts. Waist circumference will be measured with a steel tape between the rib cage and the iliac crest and hip circumference at the maximal circumference of the buttocks; waist-to-hip ratio will be calculated as waist circumference/hip circumference. Body fat percentage will be assessed via bioelectrical impedance analysis (BIA) with a wireless body composition monitor (Tanita MC-580; Tanita, Tokyo, Japan) in participants at least 3 hours after food consumption.

Clinical examinations: Blood pressure will be measured three times after the participant has been seating for 5 min. The Omron digital blood pressure monitor and appropriate cuffs sized 17–22 cm for children and 22–32 or 32–42 cm for adults will be used for this purpose and will be wrapped around the left arm with the bottom of the cuff placed about 4 cm above the elbow and the palm facing up. The blood pressure will be estimated as the average value of the second and third measurement. A full blood lipid profile will assess total cholesterol, low-density lipoprotein cholesterol, high-density lipoprotein cholesterol (HDL-C), triglycerides, non-HDL cholesterol and cholesterol to HDL ratio with the Alere Afinion AS 100 Analyzer point-of-care testing instrument. Glycated haemoglobin (HbA1c) will be measured from the second of two blood drops extracted from the fingertip previously cleaned with alcohol and pricked with a safety lancet, using the Alere Afinion AS 100 Analyzer. Haemoglobin concentration will be assessed for educators with the HemoCue Hb 301 system.

Objective measurement of physical behaviours: PA will be measured for each participant using an accelerometer (ActiGraph wGT3X-BT, Pensacola, Florida, USA) which will be worn around the hip, at all times, for 7 days (five weekdays and two weekend days), except for activities involving water contact.

Questionnaires: Information on PA during school hours and in their free time will be self-reported by children using adjusted questions from the PA Questionnaire for Children.^38^ Dietary behaviours and nutrition will be self-reported by children through a tailored, validated food frequency questionnaire^39 40^ and by educators via a 24-hour dietary recall questionnaire.^41^ The validated KIDSCREEN-10 questionnaire, European generic health-related quality-of-life questionnaire (10-domain version), will be implemented to determine children’s physical and psychological well-being.^42 43^ Where necessary, questionnaires will be translated into the home language of the children, isiXhosa or Afrikaans, and additionally explained orally by students of the Nelson Mandela University. Self-reported psychosocial health in educators will be assessed through general perceived stress (four-item Perceived Stress Scale),^44^ work-related stress (Effort-Reward Imbalance),^45^ work and family conflict (Work and Family Conflict Scale),^46^ and burn-out symptoms (Shirom-Melamed Burnout Measure^47^) questionnaires. Information about educators’ work attendance will be obtained from the schools’ attendance registers. A self-developed questionnaire will be used to assess the continuity and extent of *KaziKidz*’s implementation in the schools and will be answered by the school representative.

The support for, and integration into the school curriculum of, *KaziKidz* and *KaziHealth* sustainability will be studied by qualitative research, employing credibility, transferability, dependability, confirmability and authenticity as quality criteria when employing qualitative methods.^48^

Interviews: Information on the strengths, challenges and prospects of the *KaziKidz* toolkit implementation in the schools and the Eastern Cape school curricula will be collected via semistructured interviews. Interviewees will include principals from all participating schools (n=8), as well as representatives from the ECDoE (n=1), Provincial Teacher Development Institute (n=1) and the Nelson Mandela University (n=1). The interview schedule pertains to the perceived strengths, weaknesses, acceptance and degree of integration of the intervention programme into the school curriculum.

Focus groups: Information on community feasibility and community acceptance of *KaziKidz* and *KaziHealth* will be gathered during 16 focus group discussion (FGD) sessions of eight participants each. For *KaziKidz*, six focus groups will be organised and will include 24 parents and 24 educators from previous intervention and control schools. The sessions will last approximately 60 min. Parents and educators will be part of different groups to focus on the feasibility and acceptance of the programme at home and in schools, respectively. For *KaziHealth*, eight focus groups will include educators from all schools, whereas two other sessions will be organised with all eight schools’ principals, on the one hand, and officials from the ECDoE, on the other.

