**Methods and analysis:**

This study has an observational, longitudinal, mixed-methods design. It will follow up educators and children from the *KaziBantu* study. All 160 educators enrolled in *KaziHealth* will be invited to participate, while the study will focus on 361 *KaziKidz* children (aged 10–16 years) identified as having an increased risk for non-communicable diseases. Data collection will take place 1.5 and 2 years postintervention and includes quantitative and qualitative methods, such as anthropometric measurements, clinical assessments, questionnaires, interviews and focus group discussions. Analyses will encompass: prevalence of health parameters; descriptive frequencies of self-reported health behaviours and quality of life; the longitudinal association of these; extent of implementation; personal experiences with the programmes and an impact analysis based on the Reach, Efficacy, Adoption, Implementation, Maintenance framework.

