### Study population

Originally, in the *KaziBantu* project, both *KaziKidz* and *KaziHealth* interventions were conducted in four schools, whereas the other four participating schools were used as controls.^30^ In total, 975 children from fourth to sixth grade (aged 8–16 years) were enrolled in the study; 482 children were allocated to the intervention and 493 to the control arm. At the same time, 160 educators were enrolled among all participating schools; of those, 85 took part in *KaziHealth,* whereas 75 served as waiting-list controls.

This study will follow up children and educators from the *KaziBantu* trial. While all educators who took part in *KaziHealth* have been invited to participate in this follow-up phase, a cohort of children from the *KaziKidz* intervention, who have been identified as having an increased risk for NCDs, have been included in this study. We have defined increased risk as a child presenting at least one of the following cardiometabolic risk factors: (1) overweight or obesity, (2) elevated blood pressure or hypertension, (3) pre-diabetes or diabetes, (4) borderline or dyslipidaemia; according to age appropriate, standard classifications (table 1) and based on *KaziBantu* baseline data from July 2019. Of the 975 children who participated in *KaziKidz*, 544 were classified as «high risk» according to the above-mentioned definition. Since then, 183 children have graduated from primary school resulting in 361 eligible learners. Of those, 240 have consented to participate and have been enrolled in this follow-up study at the time this protocol was published. Of the 160 educators enrolled in the *KaziHealth* program in 2019, 105 have consented to participate and have been enrolled in this study so far.

**Table 1 T1:** Classification criteria for cardiometabolic risk in children

Risk factor	Indicators and cut-off points
Adiposity^59 60^	BMI-for-age (SD)
Overweight	>+1 and ≤+2
Obesity	>+2
Blood pressure^61 62^	SBP and/or DBP (percentiles and mm Hg)
Elevated blood pressure	≥90th and <95th or <90th but ≥120/80
Hypertension stage 1	≥95th and ≤99th or ≥130/80
Hypertension stage 2	>99th or ≥140/90
Glycaemia^63^	HbA1c (mmol/mol)
Pre-diabetes	>39 and <48
Diabetes	≥48
Dyslipidaemia^64 65^	TC (mmol/l)
Borderline	≥4.40 and 5.15
Dyslipidaemia	≥5.15

BMI, body mass index; DBP, diastolic blood pressure; HbA1c, glycated haemoglobin; SBP, systolic blood pressure; TC, total cholesterol.

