### Study design

This study represents an observational follow-up of the *KaziBantu* RCT and has been designed as a longitudinal study to investigate the long-term effects of both lifestyle interventions, *KaziKidz* and *KaziHealth*, on health parameters and behaviours of a cohort of high-risk children, as well as all educators originally included in the RCT. The overall effectiveness and sustainability of the programmes will be assessed using a mixed-methods approach, including quantitative and qualitative data collection methods and analyses (figure 1). Recruitment has started in March 2021. Assessments of health outcomes will be performed both for children and educators at two time points: April 2021 and September 2021, that is, 1.5 and 2 years post-RCT, to evaluate the maintenance of healthy, active lifestyles and its effect on an individual level. As part of the postintervention evaluation, the extent of *KaziKidz*’s implementation in the schools will be obtained from school representatives at both time points to be able to correlate the observed outcomes with continued participation in the original intervention. A qualitative analysis of the school headmasters’ experiences with *KaziKidz,* as well as of its incorporation into the schools’ curriculum with officials from the ECDoE, will take place 2 years post-RCT, in October 2021. Additionally, qualitative analyses will also be conducted with school educators on their experiences with, and incorporation of, *KaziHealth* into their lifestyles 2 years post-RCT, in October 2021. Further information on the adoption and acceptance of *KaziKidz* by educators and parents, and of *KaziHealth* by school headmasters’ and ECDoE officials will be obtained during October 2021.

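### The plan names one 17–22 cm blood pressure cuff range for children and gives no rule for a child with a larger arm, so readings in larger-armed children may be biased upward.

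*Protocol article*

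**What the plan says.** The clinical examinations paragraph of Data collection (Protocol article) describes an Omron monitor with "appropriate cuffs sized 17–22 cm for children and 22–32 or 32–42 cm for adults". It also fixes the arm, the cuff position, the resting time and the averaging of the second and third readings. It does not mention measuring arm circumference or using a larger cuff for a child.

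The abstract describes the cohort as "children (aged 10–16 years) identified as having an increased risk for non-communicable diseases". Under Study population, a child qualifies with at least one of four risk factors: "1) overweight or obesity, (2) elevated blood pressure or hypertension, (3) pre-diabetes or diabetes, (4) borderline or dyslipidaemia". Of the children enrolled in 2019, 544 met this definition; "183 children have graduated from primary school resulting in 361 eligible learners", of whom "240 have consented to participate and have been enrolled in this follow-up study" at publication.

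Clinical examinations, which include blood pressure, are among the primary outcomes. Table 1 classifies children's blood pressure by percentiles and by absolute limits of 120/80, 130/80 and 140/90 mm Hg. The follow-up assessments are in "April 2021 and September 2021, that is, 1.5 and 2 years post-RCT". The Longitudinal analysis section models changes in health parameters against personal characteristics, former trial arm, and changes in physical activity and nutrition.

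**The concern.** The sentence splits cuffs by child or adult status. Adults have two ranges joined by *or*, a choice that can only be made on arm size. Children have one, and as written a child whose arm exceeds 22 cm has no fitting cuff, although the next range starts at 22 cm and is already in the kit. Age up to 16 and selection partly on overweight both make larger arms more likely.

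A cuff too small for the arm over-reads. The error is systematic, so averaging two readings does not reduce it. It follows arm size, and hence adiposity, with two consequences. Some children could be placed in a higher Table 1 class than they belong in. And an association of blood pressure with BMI, or of blood pressure change with a behaviour that also changes body size, could be partly artefact. The adjustments named in the analysis sections (personal characteristics such as sex and socioeconomic status, school type, and clustering by school and class) do not remove an error that depends on arm size.

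**Working it through.** The documents state no arm circumference, no cuff error and no blood pressure distribution, so there is no figure of the plan's own to reproduce. The cohort count is consistent: 544 − 183 = 361 eligible. What follows is a range under stated assumptions, not an estimate.

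**Step 1. Share of children with an arm above 22 cm.** Assume arm circumference is normal with mean m and SD s. The share is 1 − Φ((22 − m)/s). Counts are out of the 240 enrolled.

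| Assumed mean (cm) | SD 2.5 cm | SD 3.5 cm | Children of 240 |
|---|---|---|---|
| 20 | 21% | 28% | 51–68 |
| 22 | 50% | 50% | 120 |
| 24 | 79% | 72% | 172–189 |
| 26 | 95% | 87% | 210–227 |

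Example: m = 20, s = 2.5 gives (22 − 20)/2.5 = 0.8 and 1 − Φ(0.8) = 0.21. The 50% row is true by construction, because the assumed mean equals the limit. Widening to a mean of 27 cm and SDs of 2.5–4 cm leaves the low end at 21% and takes the high end to 98% (m = 27, s = 2.5: 1 − Φ(−2.0) = 0.98).

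**Step 2. Effect on classification among affected children.** Assume systolic pressure has mean 108 and SD 11 mm Hg and that the small cuff adds 3, 5 or 8 mm Hg. None of these values is in the documents. The share at or above 120 mm Hg is 1 − Φ((120 − 108 − bias)/11):
- bias 0: 1 − Φ(12/11) = 13.8%
- bias 3: 1 − Φ(9/11) = 20.7%
- bias 5: 1 − Φ(7/11) = 26.2%
- bias 8: 1 − Φ(4/11) = 35.8%

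This applies only to children measured with too small a cuff, not to the whole cohort.

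**Step 3. Change since 2019, if the small cuff was used on every child both then and now.** Let p₀ and p₁ be the shares above 22 cm in 2019 and 2021. The spurious mean change is (p₁ − p₀) × bias. With SD 3 cm, 2019 means of 20, 22 or 24 cm, arm growth of 1–2 cm and a bias of 3–10 mm Hg (all assumed):
- mean 20: 25% rises to 37–50%
- mean 22: 50% rises to 63–75%
- mean 24: 75% rises to 84–91%

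The smallest result is (0.841 − 0.748) × 3 = 0.3 mm Hg and the largest is (0.500 − 0.252) × 10 = 2.5 mm Hg.

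**Step 4. Change since 2019, if the small cuff was used then and fitted cuffs are used now.** The spurious mean change is −p₀ × bias. Over the same assumptions this runs from −0.252 × 3 = −0.8 mm Hg to −0.748 × 10 = −7.5 mm Hg. Correcting the cuff can therefore produce an apparent improvement larger than the drift in step 3, so the cuff used must be known at both times.

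**The case against.** The strongest reply is that the sentence lists the kit with its typical users. It calls the cuffs appropriate, the three ranges are contiguous, the adult choice already depends on arm size, and the measurements are made by trained staff under standardised protocols that a condensed article need not reproduce. This stands in part: staff may well fit by arm size, and the documents do not show that a 17–22 cm cuff is forced onto larger arms. It does not dispose of the point, because the text states a child range with an upper limit and never says that a child may receive a larger cuff.

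Three stronger readings are tempting, and the documents support none of them.

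- *Most children will read falsely high.* This needs arm sizes that are not given. Overweight is one of four alternative criteria and its share is not stated; 16 is the top of the age range; and children who had already left primary school are excluded.
- *Entry to the cohort was distorted.* Risk status comes from 2019 baseline data, and this sentence describes follow-up measurement. The cuff practice of 2019 is not stated.
- *Blood pressure will drift upward and hide a real improvement.* The two follow-up visits are only five months apart, so growth matters mainly against 2019, and only if the same small cuff was used then. In the comparison of former intervention and control schools, drift common to both largely cancels.

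**Conclusion.** The point holds as a badly fixed measurement rule with a possible upward bias, not as a demonstrated error. Followed literally, the rule puts an undersized cuff on any child with an arm above 22 cm, for a primary outcome classified partly by absolute cut-offs. The direction of the bias and its link to adiposity are clear. The number of children affected and the size of the error cannot be derived from the document. The 21–95% range rests wholly on assumed means of 20–26 cm and SDs of 2.5–3.5 cm; its width shows how little can be said without arm measurements, but even the lowest mean considered leaves about a fifth of the children above the limit. Effects on change since 2019 are conditional on a cuff practice that this document does not report. The change is worth making because it is cheap and removes the ambiguity.

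**What to change.** - Replace the child/adult split with cuff choice by measured mid-upper-arm circumference in every participant, using the 17–22, 22–32 and 32–42 cm cuffs already in the kit.
- Record the cuff size used at each visit.
- Establish which cuff was used for each child in 2019, where this can be recovered.
- For change since 2019, add a sensitivity analysis that flags or adjusts for a change in cuff size. Do not exclude those children: they are likely to be the ones whose arms grew most, so exclusion would select on growth in a study of BMI and blood pressure change.

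The cost is one tape measurement and one data field, with no new equipment; staff already take waist circumference with a tape. The real downside is reduced comparability with 2019. If a smaller cuff was used then, moving a child to a larger one lowers the reading and could look like a lasting benefit. This should be stated wherever change since 2019 is interpreted, and if the 2019 cuff cannot be recovered, that limitation should be reported.

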### Data management

Throughout the study, personal data will be anonymised. All data will be saved on SWITCHdrive, a Swiss non-commercial cloud data storage service for institutions of higher education. Stored data will be backed up weekly and the principal investigator will supervise the content to ensure data quality. Data collected will be accessible only to authorised personnel (investigators and ethics committee members) and exclusively used for scientific research. Quantitative data will be double-entered and validated in EpiData V.3.1 and once cleaned, transferred to STATA V.15.1 for statistical analysis. Interviews and FGDs will be audiorecorded, transcribed and coded. At the end of the study, data will be anonymised and shared using the publicly accessible data repository, Zenodo.

### Data analysis

Anthropometric, clinical indicators and objectively measured PA will be characterised by means and SD, if they are close to the normal distribution, and otherwise by medians and IQRs. Data on self-reported health status, PA and dietary patterns collected in questionnaires will be treated as categorical data and described by their frequency distributions. The interview and FGD data will be analysed using qualitative content analysis,^49^ and each interview and focus group transcript will be cross-coded to locations and thematic fit. To improve intercoder reliability, two independent coders will be employed. The results of the qualitative analyses will include a taxonomy of the perceived strengths, challenges and implementation of the intervention programme.

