#### Cross-sectional analysis

Mixed linear models: Associations of continuous health and PA outcomes with personal characteristics (eg, sex, SES) will be assessed postintervention, that is, from data collected after the conclusion of the trial. It will be adjusted for the type of school (ie, intervention vs control) and potential clustering within schools and classes, respective random intercepts will be used.

Mixed logistic regression: For categorical outcome measures, after suitable dichotomisation of polytomous outcomes, associations with the same predictor variables as for the mixed linear models will be analysed post-intervention using the same random intercepts.

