### Longitudinal analysis

Mixed linear regression: Associations between longitudinal changes in continuous variables (eg, BMI) and individual characteristics, like sex and SES, will be assessed with random intercepts for schools and classes. Longitudinal changes in these outcomes will also be compared between the previous intervention and control schools after adjustment for personal characteristics. Moreover, changes in health parameters will be regressed against changes in PA and nutritional parameters. All analyses will be conducted, with and without adjustment, for the postintervention values of the respective outcomes. Also, potential associations between adjusted school-specific means of longitudinal changes in health parameters and the retrospectively assessed degrees of implementation of intervention measures in the respective schools will be assessed.

Mixed logistic regression: Longitudinal changes in categorical outcomes will be analysed by dichotomising polytomous outcomes. Analyses will be stratified according to the postintervention value of the dichotomised outcome, using mixed logistic regression models of the follow-up outcome with the same random effects structure and the same predictor variables, as previously described, for the mixed linear models. Additional analyses will be conducted by treating the postintervention and the two consequent FU outcomes as repeated measures.

To adjust for biases associated with missing data and/or lost to follow-up, inverse probability weighting will be used. Data imputation will be considered as an additional option if the drop-out rate is moderate (ie, <20%).

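### Questionnaire outcomes on health status, quality of life, activity and diet are to be categorised and dichotomised, although several are primary outcomes that could be analysed as scores or ordered categories

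*Protocol article*

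**What the plan says.** The rule is spread over several places in the protocol article.

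- **Data collection** ranks the affected variables. The primary outcomes include "self-reported and objectively measured PA, self-reported diet and self-reported psychosocial health".
- **Data collection, Questionnaires** lists the instruments. Children complete KIDSCREEN-10, adapted activity questions and a food frequency questionnaire. Educators complete a 24-hour dietary recall and four psychosocial scales, among them the "four-item Perceived Stress Scale".
- **Data analysis** fixes the data type: questionnaire data on health status, activity and diet "will be treated as categorical data and described by their frequency distributions". The abstract's list of analyses also has "descriptive frequencies of self-reported health behaviours and quality of life".
- **Cross-sectional analysis** sends these outcomes to mixed logistic regression: "For categorical outcome measures, after suitable dichotomisation of polytomous outcomes".
- **Longitudinal analysis** repeats this for change: "Longitudinal changes in categorical outcomes will be analysed by dichotomising polytomous outcomes". It adds: "Analyses will be stratified according to the postintervention value of the dichotomised outcome". A further analysis treats the postintervention and two follow-up outcomes as repeated measures, but it is described as additional.

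No ordinal model is mentioned. Mixed linear models are specified in both modelling sections, for continuous outcomes.

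**The concern.** This is a stated choice of method. An analysis plan written to follow this text would carry the choice forward.

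Once an outcome has two levels, a child whose quality of life or diet improves without crossing the cut counts as unchanged. The longitudinal models then divide the sample again by the starting level, so each model uses only part of the cohort. The repeated-measures analysis avoids that division but still works on the dichotomised outcome.

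The choice also sits badly with other uses of the same variables. The Longitudinal analysis section regresses changes in health on changes in activity and nutrition, and nutrition is measured only by questionnaire. Table 2 bases Efficacy partly on change in quality of life, and Maintenance on change in activity and diet. The study wants to measure change in these variables, and a two-level version is a coarse way to detect it. At stake is precision on several primary outcomes in a cohort of limited size.

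**Working it through.** The protocol gives no alpha, power, effect size or sample-size calculation, so there is no stated figure to reproduce. The check asks how much information a two-way cut discards.

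**Inputs from the protocol (Study population):** 240 children and 105 educators enrolled at the time of publication, in eight schools (Research setting).

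**Assumptions, not in the protocol:** an approximately normal score and a small shift for step 1; proportional odds for step 2; two equal groups and two-sided alpha 0.05 for step 3. Clustering is ignored throughout.

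**Step 1: cut score against whole score.** With a proportion p on one side of the cut, relative efficiency is φ(z_p)² / [p(1−p)].

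| Cut | Calculation | Efficiency | Loss | 240 children act like | 105 educators act like |
|---|---|---|---|---|---|
| 50/50 | 0.3989² / 0.25 | 0.637 | 36% | 153 | 67 |
| 20/80 | 0.2800² / 0.16 | 0.490 | 51% | 118 | 51 |
| 10/90 | 0.1755² / 0.09 | 0.342 | 66% | 82 | 36 |

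The educator column applies to their dietary recall, and to their psychosocial scales only if the rule is meant to cover those.

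**Step 2: cut against an ordinal analysis.** Under proportional odds, information is proportional to 1 − Σp_k³. For two levels this equals 3p(1−p).

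- Three equal categories: 1 − 3(1/3)³ = 0.889. A cut at 1/3 gives 0.667, and 0.667/0.889 = 0.75, a loss of 25%.
- Four equal categories: 0.9375. A central cut gives 0.75, a loss of 20%. A cut at 25% gives 0.5625, a loss of 40%.
- Five equal categories: 0.96. A cut at 40% gives 0.72, a loss of 25%. A cut at 20% gives 0.48, a loss of 50%.
- Five categories with 50, 25, 15, 7 and 3%: 0.856. A cut at 50% loses 12%. A cut at 97% loses 90%.
- Five categories with 10, 20, 40, 20 and 10%: 0.918. The most central cut available, at 30%, loses 31%.

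For few ordered categories and a near-central cut the loss can therefore be about 12–25%. It can be higher if no central cut exists, and much higher at an extreme cut.

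**Step 3: the same loss as power.** Take the standardised difference d that gives 80% power on the whole score: d = (1.960 + 0.842) × √(2/n per group).

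- Children, n = 120 per group: d = 0.36. Power after the cut is 60.5% (50/50), 49.4% (20/80) and 36.6% (10/90).
- Educators, n = 52.5 per group: d = 0.55. Power after the cut is 60.0%, 48.5% and 35.6%.

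**Step 4: the further split.** If 20% of the 240 children start on one side of the cut, that stratum has 240 × 0.20 = 48 children, or 48/8 = 6 per school on average. At 10% it has 24, or 3 per school. The planned random intercepts for schools and classes would have to be estimated within strata of that size.

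**The case against.** The strongest reply is that the text is narrower than it may look, and much of that reply stands.

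- A reader might infer that every questionnaire outcome is dichotomised. The Data analysis section names health status, activity and diet. The educator scales are called psychosocial health elsewhere, a term that section does not use. They may fall under health status, or they may go to the linear models; the text does not settle it. The regression on nutritional change also suggests that some dietary data are kept as quantities.
- A reader might infer that the cut is left open until the data are seen, with inflated false positives. The protocol does not say so. Cut-points are commonly set in an analysis plan, which is not shown here, so their absence from the article is not an error.
- A reader might state as fact that a third to two thirds of the information is lost. That range needs a roughly normal score and a cut between 50/50 and 10/90. The protocol gives neither.
- The Data analysis sentence is about description, and dichotomisation applies only to outcomes with several categories. The protocol does not describe how the instruments are scored. The children's activity questions and the food frequency tool are adapted, so item-level categories may be reasonable for some of them.
- Table 2 results are to be expressed as percentages, for which a dichotomy has some use.

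These points limit scope and size. They do not remove the stated choice to treat the named data as categorical and to model outcomes with several categories only after reducing them to two.

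**Conclusion.** The point holds for self-reported health status, quality of life, activity and diet. The protocol categorises these data, dichotomises outcomes with several categories, and stratifies the longitudinal logistic models on the dichotomised starting value. Self-reported activity, diet and psychosocial health are primary outcomes, so the loss falls where the study most needs precision.

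The size is conditional. For a roughly normal score the loss is about 36%, 51% or 66% at 50/50, 20/80 or 10/90, before clustering. For ordinal items with three to five categories and a near-central cut it can be about 12–25%. The effective numbers use enrolment that the protocol describes as still in progress.

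The documents do not support a claim that all questionnaire outcomes are affected, or that cut-points will be chosen after the data are seen. This is an avoidable loss of precision that should be corrected; it does not invalidate the study.

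**What to change.** Amend the analysis text as follows.

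1. Analyse multi-item scale scores and intake quantities as continuous outcomes in the mixed linear models already specified, transformed if skewed.
2. In the longitudinal models for these outcomes, adjust for the postintervention value and do not stratify on it. The linear section already foresees analyses with and without that adjustment.
3. Use mixed ordinal logistic regression where responses are truly ordered categories, with the same random intercepts.
4. Keep dichotomies only as supportive analyses, at an established threshold fixed before the follow-up data are examined.
5. State that the same rules apply to the educators' stress, effort-reward, work-family conflict and burn-out scales, which the present text leaves unclear.

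No new data are needed. The cost is slightly more modelling work, and checks of distributional and proportional-odds assumptions.
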